### 6.3 Claim 3: IBS Granger-causes reciprocal conversational behaviors

While the previous analyses give a sense of the relationship among time courses, they do not illuminate the direction of influence between one time course and another. To that end, we will compute Granger causality (Granger, 1969). Our prior work already shows that rapport Granger-causes increasing entrainment in some conversational behaviors, and particularly in speech rate (Sinha and Cassell, 2015b). It has also been employed to show that dual brain stimulation improves collaborative learning via the mechanism of spontaneous movement synchrony (Pan et al., 2021). Here we seek to understand whether rapport Granger-causes IBS or vice-versa and, subsequently, whether conversational behaviors Granger-cause IBS or vice-versa. Given the slower time scale of fNIRS signals, a relatively large time window will be used. That is, we hypothesize that it might take as long as 5 seconds for one of these phenomena to Granger-cause the other. The Granger causality approach relies on the accuracy of one time series in predicting the future behavior of another time series. In particular, we determine whether time series *A* (e.g., IBS) Granger-causes time series *B* (e.g., rapport or a relevant behavior feature) by assessing whether incorporating past observations of time series *A* in a linear regression model of time series *B* and time series *A* reduces prediction error compared to a model containing only previous observations of time series *B*.

In recent neuroscience studies, Granger causality has demonstrated the ways in which men in elderly couples Granger-cause competitiveness in their spouses in the first half of a competitive game, while there is no causality in either direction in the latter half of the game (Zhang et al., 2023). In recently-published research, it has been shown that mutual non-verbal behaviors, particularly mutual smiles, laughter, and body movement anticipate and Granger-cause IBS, even in the absence of a specific task (Koul et al., 2023). However, in that experiment participants were *required* to look at one another, and so spontaneous mutual gaze behaviors were not evaluated. In the current work, we compute the pairwise conditional G-causality in both directions. If no causality is evident in either direction, our prior work motivates looking at the causal relationships between the mutual behaviors previously revealed to be influential in rapport-building and IBS (described above). Therefore, in this case, time series *A* and time series *B* will refer to the average IBS value for every 30-second epoch and the rapport values/occurrence of a relevant behavior for each 30-second slice. The statistical significance will then be assessed through an F-test under the null hypothesis that one time series does not Granger-cause the other. This analysis can reveal both unidirectional influences, wherein one time series significantly Granger-causes the other (i.e., one time series tends to lead the other), and bidirectional influence, indicating that both time series Granger-cause one another in a reciprocal manner. Indeed, if past values of the time series *A* help improve the prediction of time series *B*, and at the same time, past values of time series *B* also help improve the prediction of time series *A*, then bidirectional influence is present.

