***Claim 1: Conjunctions of conversational behaviors across modalities better***
***predict IBS*. **Understanding how social bonds among peers are reflected in IBS requires the integration across the conversational modalities: verbal, non-verbal, and paraverbal, rather than looking at one single conversational modality or behavior (such as eye gaze).***Claim 2: IBS and rapport evolve similarly across time*. **We use Dynamic Time Warping to quantify the temporal similarity between the two representations of social connectedness, through dyadic measures at the neural and psychological level.***Claim 3: IBS Granger-causes reciprocal conversational behaviors*. **Beyond temporal similarity, we expect that IBS is a precondition of successful dyadic conversational behavior and thus the emergence of rapport.***Claim 4: Not all rapport is productive*. **We introduce the notion of “productive rapport”; that is, rapport that leads to learning gains in educational tasks, in contrast to unproductive rapport that is detrimental to learning. We therefore run analyses that examine whether there is a inverted U-shaped curve between rapport-building and performance.***Claim 5: Rapport-building is a process that takes time*. **Rapport is rarely built in a 1-h session, and so we argue that a study design must illuminate the time course of rapport at both the time scale of an hour during a single interaction, and of several weeks in a longitudinal design.***Claim 6: Brain regions evolve with age*. **It is well-known that the brain evolves across the period of middle childhood and beyond (Lebel and Beaulieu, 2011). We argue that with age we will find more reciprocal conversational behaviors, as children become more able to participate in interpersonal synchrony, and increasingly able to develop abstract shared mental representations with others. We predict that this will lead to greater IBS, and a progressive shift in activation from rTPJ to PFC.

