Bringing these axes together we predict that we will find stronger and more generalized IBS where conversational behaviors (verbal, non-verbal, and paraverbal) are reciprocal. That is, in cases of mutual eye gaze and mutual smiles, reciprocal self-disclosure, and entrainment (sometimes called alignment) where the pattern of behavior is increasingly similar between members of a dyad, such as increasingly similar speech rate. We predict that these patterns of dyadic behavior will be followed by increased IBS and that, in turn, this will allow us to distinguish between productive and unproductive rapport on the basis of IBS that follows dyadic behavior. That is to say, IBS will be present in more regions of interest, and will be stronger, when it co-occurs with high rapport that accompanies (and just precedes) learning gains.

Here, due to its non-invasive nature, high safety profile, reduced sensitivity to participants' motion, and higher spatial resolution than EEG, the fNIRS technique can play an important role (Providência and Margolis, 2022). Its reduced sensitivity to movement makes it ideally suited to investigate the naturalistic phenomena that make up social interaction (Pinti et al., 2020), and particularly social interaction among children, who may find it difficult to stay completely still. While EEG captures responses to individual events at a high temporal granularity (single syllables, articulation of the face), fNIRS integrates over these to reveal the different brain region that are more or less active on the timescale of seconds, and therefore allows us to focus on overall task components, rather than events at the sensory modality level of resolution.

An earlier study conducted by Rabinowitch and Knafo-Noam (2015) found that ratings of closeness were higher for children who participated in a synchronous finger tapping exercise, a result thought to illustrate the positive effects of synchronous (non-conversational) interaction in children, but given the increased focus in neuroscience on actual social interaction, and the tools available to do so, it is time to study IBS in child dyads engaging in actual social interaction, with an eye toward better understanding and better implementation of supporting technologies.

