### 6.1 Claim 1: conjunctions of conversational behaviors across modalities better predict IBS

We argue that focusing on a single conversational behavior (such as eye gaze) under-estimates the complex interplay among modalities in their relationship to neural synchrony. To adduce evidence for this claim we will leverage Long Short-Term Memory (LSTM) networks to predict IBS on the basis of temporal sequences of behavioral data (see Table 1 for further details on the behavior types and variables). Since conversational behaviors are likely to lead to IBS with a certain lapse of time, we insert a 1 to 10 second time lag between the sequences of conversational behaviors and the IBS (Chang et al., 2022). The dataset will be structured into sequential behavioral data over time, each associated with a 30-second interval IBS value and normalized through a Min-Max scaling technique, ensuring consistent proportions across all features, while preserving the original distribution of the data.

**Table 1 T1:** Data sheet.

**Level of data type**	**Modality**	**Dyadic status**	**Specific variables**	**Notes**
Conversational Behavior	Verbal	Non-reciprocal	◾Self-disclosure	Number of behaviors per 30 second epoch.
			◾Reference to shared experience	
			◾Praise	
			◾Teasing	
		Reciprocal	◾Mutual self-disclosure	
			◾Mutual reference to shared experience	
			◾Mutual teasing	
	Paraverbal	Non-reciprocal	◾Pitch shift	
			◾Shift in speed of speaking	
			◾Shift in loudness	
		Reciprocal	◾Mutual pitch shift	
			◾Mutual shift in speech rate	
			◾Mutual shift in loudness	
	Nonverbal	Non-reciprocal	◾Smile	
			◾Head nod	
			◾Gaze at other person	
		Reciprocal	◾Mutual smile	
			◾Mutual head nod	
			◾Mutual eye gaze	
Rapport State		Rapport rating (1–7) for each 30 second interval for each dyad		
Educational Performance		Every week	Task 1–3, week (with x = 1–6)	◾Number of hypotheses per weekly 8–10 min read-out
				◾Number of pieces of evidence per 8–10 min weekly read-out
IBS				◾Right hemisphere ROIs

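### Section 6.3 tests whether IBS or behaviour comes first without correcting IBS for haemodynamic delay, so the direction is biased and not identified

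*Protocol article*

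**What the plan says.** Section 3 (Framework) gives the expectation behind Claim 3: "we expect that IBS is a precondition of successful dyadic conversational behavior and thus the emergence of rapport". Section 6.3 tests it in both directions ("we compute the pairwise conditional G-causality in both directions") with an F-test, and allows for a bidirectional result. On the slow signal it says: "Given the slower time scale of fNIRS signals, a relatively large time window will be used". On the size of the lag: "we hypothesize that it might take as long as 5 seconds for one of these phenomena to Granger-cause the other". The two series are "the average IBS value for every 30-second epoch and the rapport values/occurrence of a relevant behavior for each 30-second slice".

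IBS is wavelet coherence of haemoglobin concentrations over 0.01 to 0.15 Hz (sections 5.2 and 5.2.2). Section 5.2.1 has the data cut into 30-second epochs before IBS is calculated. Section 6 aligns the streams by recorded event codes. None of these sections names a time shift or a deconvolution.

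Two other statements bear on order. For Claim 1, section 6.1 says "we insert a 1 to 10 second time lag between the sequences of conversational behaviors and the IBS", with behaviour first. The closing part of section 3 says "We predict that these patterns of dyadic behavior will be followed by increased IBS", which is the opposite order to Claim 3.

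**The concern.** Event codes align the recording clocks, not the physiology. Behaviours, and the 30-second slices on which rapport is rated, sit on the video clock. IBS sits on a blood-flow clock that runs late, always in the same direction. A larger window lets the model look further back but leaves that offset in place. The 5 s in section 6.3 is a model lag allowed in either direction, not an alignment offset.

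Direction is the only thing section 6.3 adds to the association analyses. If the offset is as large as the lead being sought, the answer depends on vascular delay rather than on the interaction. The document also predicts both orders in different places, so a biased test could be read as support for either.

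**Working it through.** **1. Series length (the plan's own figure).** 8-10 min / 30 s = 16-20 epochs per session; x 2 dyadic sessions = 32-40; x 6 weeks = 192-240. This agrees with section 5.4.

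**2. Order on the recorded clock.** Let L be the true neural lead over behaviour and H the haemodynamic delay. Behaviour appears at L and IBS at H, so recorded IBS leads only if L - H > 0. Section 6.3 puts L at 5 s or less. H is an assumption:

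| L | H = 4 s | H = 6 s | H = 8 s |
|---|---|---|---|
| 2 s | -2 | -4 | -6 |
| 3 s | -1 | -3 | -5 |
| 5 s | +1 | -1 | -3 |

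The epoch is 30 / 5 = 6 times the longest hypothesised lead, so how much of this offset survives averaging has to be simulated.

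**3. Simulation without correction.** Neural synchrony is AR(1) with a 20 s time constant. Behaviour is the same signal L seconds later. IBS is the signal convolved with a response peaking at H = 6 s. Both are averaged to 30-second means with noise (signal-to-noise 1 to 4). The test is a lag-1 Granger F-test at alpha 0.05 on 240 pooled epochs.

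| L | L - H | Behaviour leads only | IBS leads only |
|---|---|---|---|
| 1 s | -5 s | 70-91% | 1-3% |
| 2 s | -4 s | 61-88% | 3-9% |
| 3 s | -3 s | 50-80% | 8-19% |
| 5 s | -1 s | 32-41% | 29-31% |

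Reference with no delay (H = 0, L = 2 s): IBS only in 48-75%.

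**4. Same simulation, IBS moved back 6 s (signal-to-noise 1).**

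| L | IBS only, before and after | Behaviour only, before and after |
|---|---|---|
| 2 s | 9% to 53% | 61% to 13% |
| 3 s | 19% to 64% | 50% to 7% |
| 5 s | 29% to 83% | 32% to 2% |

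**5. Sensitivity, uncorrected, H = 6 s.**
- One session of 20 epochs: neither direction in about 79-89% of runs.
- 1-second data with 5 lags, L = 2 s: behaviour only in 46-93%, the rest both.
- Time constant 5, 20 or 40 s (L = 2 s, signal-to-noise 2, 240 epochs): behaviour only 33%, 76%, 42%; IBS only 2%, 7%, 3%. At 5 s most runs (62%) show neither; at 40 s about half (53%) show both.

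**6. How coherence is computed.** The band 0.01-0.15 Hz means periods of 1/0.15 = 6.7 s to 1/0.01 = 100 s.
- Coherence inside each pre-cut epoch (section 5.2.1), L = 3 s, H = 6 s: mean t was -1.0 for IBS to behaviour against 10.1 for behaviour to IBS. After a 6 s shift it was 6.0 against 3.7.
- Coherence over the whole phase: the net bias ran towards IBS leading, and with no true lead the shift strengthened that false lead.
- Symmetric smoothing as a stand-in for whole-phase coherence (SD 20 s, assumed; L = 2 s, no shift): behaviour only in 2-6%, mostly both or IBS only.
- No true lead, smoothing SD 10 or 20 s, 528 phases: shifts of 4, 6 and 8 s each gave a positive IBS-to-behaviour effect in 100% of runs.

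**The case against.** The strongest reply is that wavelet coherence draws on signal before and after each time point. An epoch's IBS would then contain information from the next epoch, which pushes towards IBS leading. This stands for coherence computed over the whole phase and then averaged by epoch. It does not fit section 5.2.1, where segmentation comes first; under that order the bias towards behaviour leading remains (step 6).

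A second reply is that an alignment constant is detail an article leaves to the full plan. That would hold if section 6.3 were silent. It names the problem and states a remedy, and the remedy does not act on the bias.

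A third reply is that a shift alone can manufacture support for Claim 3. This stands: where smoothing crosses epochs, agreement over several shifts would confirm a lead that does not exist. Stability over the range is therefore not a sufficient safeguard.

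A reader might infer that any true IBS lead will be reported as behaviour leading. The documents do not support that. Reversal in 100% of runs appears only with low noise, pooling of 44 dyads x 12 phases = 528 series, and counting of positive effects only. Section 6.3 states neither the pooling nor a sign rule. Under a plain two-sided test, both directions were significant in 100% of runs in that setting, which the plan would report as bidirectional. At signal-to-noise 1 with the same pooling, a 3 s lead gave both directions in 88% and behaviour only in 12%.

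**Conclusion.** The point holds as biased and unidentified direction, not as certain reversal. With coherence inside pre-cut epochs, the uncorrected delay moves evidence towards behaviour leading IBS, against Claim 3. It can reverse the direction when the neural lead is well below the delay: for a 3 s lead and a 6 s delay, 50-80% of runs against 8-19%. Within about 1 s of the delay the result is close to a coin toss. Single-session or noisy data often give neither direction or both. Whole-phase coherence biases the test the other way.

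The figures rest on an assumed delay of 6 s within a plausible 4 to 8 s, on simulated noise and autocorrelation, and, in steps 3 to 5, on a simplified model of IBS. None of these values is in the document. That 30-second epochs are coarse for a 5 s lead is a separate weakness, which the delay correction does not cure.

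**What to change.** - Before cutting the epochs used in section 6.3, move the fNIRS time axis back by one delay fixed in advance, and repeat over a fixed range (for example 4, 6 and 8 s). Use the same alignment for rapport and for behaviours.
- State that coherence for section 6.3 is computed within epochs, as section 5.2.1 has it.
- Run the identical pipeline on simulated or surrogate data with no lead, to show that the test does not favour a direction.
- Claim a direction only if it is the same over the whole range and exceeds the no-lead reference. Otherwise report association without direction.

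The cost is one pre-processing step, a few reruns and the calibration run. Some results will be reported as direction undetermined. A 30-second epoch also holds less than one cycle of anything below 1/30 = 0.033 Hz, so within-epoch coherence says little about the lowest part of the planned band; the plan should acknowledge this.

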While we sometimes refer to feeling instantly “in sync” with somebody we have just met, for the most part rapport fundamentally has to do with the change of a relationship over time. In order to assess the changes in rapport over the course of the 6 weeks of the longitudinal experiment, we will rely on the concept of utopy (Sinha, 2016). Prior work has shown that statistical summaries such as a measure of central tendency or proportion of high and low ratings of rapport, collapse the temporal dimension and are not as robust as more stochastic-based models which capture the evolution of rapport over time (Sinha, 2016). We will thus fit a Markov chain of order 1 to the sequence of 16 to 20 rapport ratings for each session (8–10 min), the sequence of 32 to 40 rapport ratings over the two dyadic sessions (collaboration and open-ended chat) and the 192 to 240 rapport ratings for the two dyadic sessions over the entire 6 weeks, and use the resulting transition probability matrix to generate a measure of the “utopy,” or likelihood of the dyad being in a high-rapport state. This likelihood is calculated as the sum of each transition probability weighted by the distance of the transition (Sinha, 2016; Madaio et al., 2017b). This allows us to assess the temporal dynamics of rapport.

As described above, we will also ask children after each interaction to rate their preferred closeness and feelings of closeness to their partner.

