### 6.2 Claim 2: IBS and rapport evolve similarly across time

After describing how we will assess the relationship between reciprocal conversational behaviors and IBS, we now turn to the relationship between the psychological state of rapport, as brought about by conversational behaviors, and IBS. To achieve this, we will establish a behavior analysis pipeline that preserves the temporality of the different data streams, while highlighting the relationship among them. Because the time scales of different behavior streams may differ, it can be challenging to analyze the potentially non-linear relationship between rapport and neural synchrony. Here we will therefore set up a pipeline using Dynamic Time Warping (DTW), a powerful method that has been previously used to compare the dynamics of brain activation between the time series of two participants (Azhari et al., 2019). In our own prior work, DTW has also been used to characterize how the conversational strategy usage for each partner in a dyad is aligned in time with that of the other partner (Sinha and Cassell, 2015b), allowing us to assess entrainment, and influence of each member of the dyad on the other. The application of non-linear transformations as carried out by DTW is particularly advantageous for the relatively slow fNIRS time scale compared to the observed behavioral events (Quaresima and Ferrari, 2019). The DTW method causes specific changes in the timing of events in two different data streams. These alterations are made in such a way as to allow for the best possible alignment or matching of the two time-series (Berndt and Clifford, 1994). DTW then provides a measure called “warping distance”, which helps us compare and quantify how different the two sequences are from one another, based on the changes needed to align them. Smaller warping distance values mean that the sequences are more similar, while larger values indicate greater dissimilarity.

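### Section 6.3 defines the Granger test with two series but calls it pairwise conditional without naming a conditioning series; under the plan's own premises the two-series rapport–IBS test can exceed its nominal error rate

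*Protocol article*

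**What the plan says.** All of the test description is in section 6.3 of the protocol article.

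- **Rule.** A Granger-causes B if including the past of A in a regression that already holds the past of B "reduces prediction error compared to a model containing only previous observations of time series" B. No third series appears in either regression.
- **Name.** For this study, "we compute the pairwise conditional G-causality in both directions".
- **Series.** A and B are "the average IBS value for every 30-second epoch and the rapport values/occurrence of a relevant behavior for each 30-second slice".
- **Inference.** "The statistical significance will then be assessed through an F-test under the null hypothesis that one time series does not Granger-cause the other". This null again involves two series only.
- **Questions.** The aim is to learn "whether rapport Granger-causes IBS or vice-versa and, subsequently, whether conversational behaviors Granger-cause IBS or vice-versa".

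Two other sections say how the three streams are expected to be related. Section 6.2 refers to "the psychological state of rapport, as brought about by conversational behaviors, and IBS". Section 6.1 expects behaviours to lead to IBS after some time, and so "we insert a 1 to 10 second time lag between the sequences of conversational behaviors and the IBS". Section 6.2 also plans a mediation analysis with rapport between reciprocal behaviours and IBS.

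**The concern.** A conditional Granger test needs the past of at least one further series in both the restricted and the full regression. With only A and B in play there is nothing to condition on, and the test reduces to the two-series rule. So either the word conditional does not belong, or the conditioning series has not been stated. Two analysts following section 6.3 could run different tests.

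The difference matters here because of what the article itself expects. If behaviour raises rapport and, somewhat later, IBS, then past rapport carries information about past behaviour. It can therefore improve the prediction of IBS even when rapport has no effect on IBS. The two-series test would report that rapport leads IBS, which is one of the directional questions that section 6.3 sets out to answer.

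**Working it through.** **Series lengths.** Section 5.4 gives "the sequence of 16 to 20 rapport ratings for each session". This reproduces: 8 min × 60/30 = 16 and 10 min × 60/30 = 20 (midpoint 18). Two dyadic sessions give 32–40 (midpoint 36).

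**Test.** The statistic is F = [(RSS_restricted − RSS_full)/q] / [RSS_full/(usable epochs − parameters)], with q = 1 at lag 1. Section 6.3 gives neither alpha nor lag order; 5% and one lag are assumed.

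- Two-series: restricted is IBS(t) on a constant and IBS(t−1); full adds rapport(t−1).
- Conditional: the same, with behaviour(t−1) in both.

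**Model 1 (epoch scale).** Autoregression 0.4 in each series, unit-variance noise and loading k are all assumed. There is no rapport–IBS link.

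- behaviour(t) = 0.4·behaviour(t−1) + e
- rapport(t) = 0.4·rapport(t−1) + k·behaviour(t) + e
- IBS(t) = 0.4·IBS(t−1) + k·[(1−w)·behaviour(t) + w·behaviour(t−1)] + e

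Here w is the share of the effect that falls in the next epoch. A whole-epoch delay is w = 1. For the 5 seconds that section 6.3 gives as a possible upper delay, w = 5/30 = 0.17.

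False rapport-to-IBS findings, two-series test:

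| Delay | k | 18 epochs | 36 epochs |
|---|---|---|---|
| 5 s | 0.3 to 0.8 | about 7–11% | about 7–13% |
| One full epoch | 0.3 / 0.5 / 0.8 | 7 / 15 / 40% | 10 / 27 / 70% |

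With behaviour's past in both regressions, the rate is about 4–7% in these runs.

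**Model 2 (behaviour at 1-second resolution, averaged to 30 s; noise SD 0.7; lag 1).** False rapport-to-IBS findings at 20 / 40 epochs, two-series test:

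| Delay | No behaviour autocorrelation | Time constant 30 s |
|---|---|---|
| 1 s | 4 / 6% | 11 / 21% |
| 5 s | 9 / 14% | 18 / 41% |
| 10 s | 19 / 33% | 37 / 68% |

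Conditioned on behaviour, this direction is about 4–6% throughout.

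**Where the two-series test is sound.** With no common driver it rejects in about 4–5%. If behaviour is not autocorrelated and reaches both series at the same lag, it also rejects in 4–5%. If IBS responds an epoch before rapport, the false finding is mainly IBS-to-rapport (49% / 86% at 20 / 40 epochs).

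**Where conditioning falls short.**

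- *Lag order too short.* If rapport responds at lag 1 and IBS at lag 2 but one lag is fitted, the conditioned rate is 39% / 75% at 20 / 40 epochs. Two lags bring it to 6% at 40 epochs.
- *30-second averaging.* In Model 2 (time constant 30 s, 10-second delay), the conditioned IBS-to-rapport test rejects in 9% / 13% at 20 / 40 epochs, against 5% / 5% for the two-series test.

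**Conditioning the behaviour–IBS test on rapport.** Suppose behaviour raises rapport in the same epoch and rapport raises IBS in the next, a true mediated effect. At k = 0.8 and 36 epochs, the unconditional test detects behaviour-to-IBS in about 85% of series and the rapport-conditioned test in about 4%.

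**The case against.** The mismatch can be read as mild. The first passage may be a general introduction to the method and the second the name of the measure actually used, with the conditioning set left to a fuller plan. That would excuse a missing list of series. It does not settle the matter, because the detailed description after the name still involves only A, B and a two-series null.

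The objection to size is stronger, and much of it stands. The largest rates need the whole effect of behaviour to arrive 30 seconds later, whereas the article speaks of 1 to 10 seconds in section 6.1 and up to 5 in section 6.3. At 5 seconds Model 1 gives only a modest excess. Model 2 gives more, but only with assumed autocorrelation. The loadings are assumed in both.

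Three stronger readings are tempting, and the document does not support them:

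- *The two-series test always produces false causation when behaviour drives both.* It does not: same-lag driving without autocorrelation stays near 5%.
- *Error rates near 100% over six weeks.* These come from treating the 192–240 points as one series. Section 5.4 uses that length for the rapport Markov chain. Section 6.3 never says the Granger test joins sessions, and a lag across a week's gap has no meaning.
- *Every Granger test should be conditional first.* For behaviour–IBS this would remove an effect that section 6.2 plans to study through mediation. Total and direct precedence are different questions.

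**Conclusion.** The concern holds in a limited form. Section 6.3 describes a two-series test and names a conditional one, and the passages must be reconciled. Under the article's premise that behaviour precedes both rapport and IBS, the two-series rapport–IBS test can exceed its nominal 5%. In the lag-1 model with autoregression 0.4 and k = 0.3–0.8, the excess is small at a 5-second delay (about 7–11% per phase, 7–13% per week). It becomes large (up to about 40% and 70%) only if the whole effect falls one epoch later. The 36-epoch figures also assume that the two sessions of a week are analysed as one series. All sizes rest on assumed loadings, autocorrelation, delay, lag order and alpha, so they show what could happen rather than predict this study's error rate.

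**What to change.** In section 6.3, give one definition for each question.

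- **Rapport–IBS, both directions.** Include the past of the reciprocal behaviour series in both the restricted and the full regression. Name those series, and state alpha and a lag order that covers the expected delay. Report the two-series result as a sensitivity analysis.
- **Behaviour–IBS.** Keep the unconditional test as the total-effect result. Report the rapport-conditioned test beside it as the direct effect.

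The cost is one regressor per conditioning series per lag, which matters in short phases. With 18 epochs and one lag there are 17 usable points. The two-series full model leaves 17 − 3 = 14 residual degrees of freedom, and one conditioning series leaves 13. All nine reciprocal behaviours in Table 1 would leave 17 − 12 = 5. At two lags they would need 1 + 2 + 2 + 18 = 23 parameters for 16 points, which cannot be fitted. A short prespecified list or one combined reciprocal count is therefore needed.

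The text should also say that conditioning does not remove all bias from 30-second averaging, notably in the IBS-to-rapport direction, so a conditional finding there needs a cautious reading.

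### Section 6.3 contradicts itself on whether the test of Claim 3 (IBS Granger-causes reciprocal behaviours) is unconditional or run only after a null first step

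*Protocol article*

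**What the plan says.** The hypothesis is stated twice. The heading of section 6.3 is "Claim 3: IBS Granger-causes reciprocal conversational behaviors". Section 3 (Framework) gives the reasoning under Claim 3: "we expect that IBS is a precondition of successful dyadic conversational behavior and thus the emergence of rapport".

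The first paragraph of section 6.3 sets the questions in order: "whether rapport Granger-causes IBS or vice-versa and, subsequently, whether conversational behaviors Granger-cause IBS or vice-versa". No condition is attached to the second question. The same paragraph describes the outcome series as "e.g., rapport or a relevant behavior feature".

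The second paragraph turns to what will be done: "In the current work, we compute the pairwise conditional G-causality in both directions". The pair of series is not named in that sentence. The next sentence begins "If no causality is evident in either direction, our prior work motivates looking at the causal relationships between the mutual behaviors" and goes on to IBS, limiting the behaviours to those that earlier work found influential for rapport. The series for this case are then the epoch means of IBS and "the rapport values/occurrence of a relevant behavior for each 30-second slice". An F-test follows, with no significance level given.

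**The concern.** Mutual behaviours are the reciprocal behaviours of Claim 3: every row marked reciprocal in Table 1 is a mutual behaviour. The claim's own hypothesis is therefore an unconditional second step in one paragraph and a step that depends on a null result in the next. Nothing in the section reconciles the two.

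The condition also works against the theory. Section 3 expects IBS to lead to dyadic behaviour and through it to rapport. If that is right, a rapport–IBS link is likely to be found, and the second paragraph taken literally would then leave the test of Claim 3 undone.

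No other analysis fills the gap. The LSTM in section 6.1 predicts IBS from earlier behaviour, and the mediation model in section 6.2 runs from reciprocal behaviour through rapport to IBS. Direction is also unsettled within the article: section 3 predicts that dyadic behaviour precedes a rise in IBS, and section 6.1 assumes that behaviour leads to IBS after a lag. Only the Granger test in section 6.3 can set Claim 3 against those statements.

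**Working it through.** The article gives no figure for this sequence, so there is none to reproduce. The check has two parts.

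**1. The two paragraphs of section 6.3 side by side**

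| | First paragraph | Second paragraph |
|---|---|---|
| Rapport and IBS | First question, both directions | Appears to be the first step, both directions (pair not named) |
| Behaviours and IBS | Second question, both directions, no condition | Mutual behaviours, looked at if the first step shows no causality |

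If the first step is rapport–IBS, a positive result there means the second paragraph never calls for the Claim 3 test, while the first paragraph still does. An analyst cannot follow both.

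**2. Illustration of the condition, taken literally**

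Inputs:
- Alpha 0.05 per test: assumed. The only alpha in the article is 0.05 in section 4.1, for the ANOVA sample size.
- Independent tests: assumed.
- Stop rule: assumed. Any one significant first-step result cancels the mutual-behaviour test.
- Two directions: section 6.3.
- Number of IBS series: not stated for this test. One if a single average is used; three if only the right-hemisphere regions shown in Table 1 are used; six if all regions of section 5.2.2 are used.

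*No true rapport–IBS link.* P(Claim 3 test cancelled by a false positive) = 1 − 0.95^(2k), with k IBS series:
- k = 1: 1 − 0.95^2 = 0.0975, about 10%
- k = 3: 1 − 0.95^6 = 0.265, about 26%
- k = 6: 1 − 0.95^12 = 0.460, about 46%

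*One direction truly present, one pair.* P(Claim 3 test reached) = (1 − power) × (1 − 0.05):
- power 0.50: 0.50 × 0.95 = 0.475
- power 0.80: 0.20 × 0.95 = 0.19
- power 0.95: 0.05 × 0.95 = 0.0475, about 0.05

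*Both directions truly present, one pair.* P(reached) = (1 − power)^2: 0.25, 0.04 and 0.0025 at the same three powers.

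The stronger the rapport–IBS link, the less often the test of Claim 3 is reached.

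**The case against.** The strongest reply is that the unconditional test is already in the plan. The first paragraph lists behaviours and IBS as a step to be done in any case and names a behaviour feature as a possible outcome series. The wording of the second paragraph is also soft: prior work motivates a look, which is weaker than an exclusive rule. The series defined for the conditional case still include rapport, which fits loose drafting better than a deliberate two-stage procedure. One could read it as testing all behaviours first and giving the previously influential mutual ones a focused second look if nothing appears.

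Much of this stands. A reader might infer that Claim 3 is tested only as a fallback; the first paragraph does not support that. That the first step is rapport–IBS is an inference from the order of the questions. The kinder reading, however, does not remove the conflict, because the set placed behind the condition is still the set that Claim 3 is about.

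A reader might also infer that the conditional step is an uncontrolled search in which chance findings are almost certain, for example 9 reciprocal behaviours × 6 regions × 2 directions = 108 tests. The article does not support that count. It states neither an alpha nor a region-by-region analysis for this claim, and it limits the step to behaviours found influential before. Multiplicity detail is also commonly left to an analysis plan, so its absence here is not a fault.

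**Conclusion.** The point holds as an internal contradiction. Section 6.3 makes the behaviour–IBS test unconditional in its first paragraph and makes the mutual-behaviour part of it depend on a null result in its second. Followed literally, the second paragraph can leave Claim 3 untested just when a rapport–IBS link is found, and no other planned analysis covers the IBS-to-behaviour direction.

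The contradiction itself rests on the text alone. The size does not: the 10% to 46% range and the probabilities of reaching the test depend on the assumed alpha, independence, stop rule and number of IBS series, and on rapport–IBS being the first step. They show which way the condition pushes and are not estimates for this study.

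**What to change.** In the second paragraph of section 6.3, delete the condition on finding no causality. State that IBS to reciprocal behaviour, and the reverse direction, is the test of Claim 3 and is run whatever the rapport–IBS result. Report rapport–IBS causality as a separate question and name the pair of series for each test.

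This is a change of wording and needs no new data. It should be settled before the 9–10-year-old dyads are analysed, since section 4.2 expects those results to be published first.

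Optionally, the false discovery rate correction named for Claim 6 in section 6.6 could be extended to this set of tests. Its cost is a stricter threshold for each individual link.
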